### Outcome measures (health care consumption data)

The IMA uses algorithms to identify patients for the study population and to deliver data relevant to the research questions. These data identified by the NN of all patients in the study population (see 2.3) and NIHDI-numbers of their GPs will be coded by an innovative coding strategy, as explained more in detail in 2.9. This data collection will end the 31st of December 2018, two years and nine months after the end of Phase 6 (see Fig. 1).

#### Primary outcome: reduction of hospital death rate

The primary outcome of this study is a reduction of all hospital deaths from 50 % [30, 31] to 35 %. In Belgium, about half of people die in the hospital, including about 5 to 10 % of deaths in a palliative care unit [30, 31]. Through health care consumption data, it can be known which percentage of the deceased of a GP practice, in a certain period died at home, in a nursing home, in a hospital or elsewhere.

#### Secondary outcome: use of services

The secondary outcome is directing use of services towards quality of life in the last year of life. The ideal health care spending pattern is considered to be palliative home care (more contacts with GPs than with hospital doctors, …), with more use of symptomatic medication than of medication with a clear life prolonging intention and reduction of stressful diagnostic and therapeutic procedures. Indicators here, available by the IMA, are:Contacts of patients with primary care: GPs, home care nurses, physiotherapistsSupport of patients by palliative home care: palliative forfeit, palliative home care teamsEmergency department visits with or without GP referralLength of stay in hospital, nursing home, or palliative care unitUse of medication with clear curative or life prolonging intent (e.g. statins)Use of symptom medication (e.g. morphine, antidepressants)Selection of diagnostic procedures: common lab tests, imaging proceduresSelection of therapeutic procedures: blood transfusion, ascites paracentesis, etc.Health care consumption costs.

### Monitoring of implementation, quality of care and quality of life (GP and patient surveys)

Participating GPs, patients and relatives will fill periodical web-based surveys on illness trajectory and different aspects of care quality. These surveys will be collected via a secured electronic data collection system. All surveys have been drafted and piloted in Dutch, and have been back-and-forth translated to French; they are available on request.

To identify uniquely all patients involved, their NN numbers are used. To guarantee confidentiality of these personalized research data, the unique NN numbers will be coded electronically by eHealth, the health care data coding agency of the Belgian federal government (see 2.9 for more details). Doing so, re-identification of patients by the analysts is impossible.

The professional NIHDI number of participating GPs number is used for the data collection and coded by similar procedures during the data handling process, making re-identification of the health care professional impossible.

This data collection strategy will end the 31st of December 2016, nine months after Phase 6 (see Fig. 1).

#### Monitoring level of CPPPC implementation

On the regional level, the number of GPs reached by educational sessions and regional platform meetings will be measured, besides the quality of these educational sessions as perceived by attending GPs and the number of GPs interested to participate.

Participating GPs will be asked (1) to fill an 11-item baseline survey including personal characteristics and the 10 days practice denominator and (2) to include eligible patients for the study, i.e. being older than 45 years and having a ‘positive surprise question’ according to the GP [24]. For all included patients, the GP will fill a baseline survey on the patient’s medical condition based on the validated Supportive and Palliative Care Indicator Tool (SPICT)(version June 2013) [32]. To reduce the barrier of administrative overload for GPs, in this baseline survey the GP can choose whether a single-item survey (PPSv2) will be filled for this patient: if yes, this patient is called a ‘focus’-patient.

Per ‘focus’-patient, the GP fills a single-item survey (PPSv2) monthly, or weekly if the PPSv2 score is becoming 30 %, or less (when the patient gets weak and life expectancy decreases more) [33]. When a participating patient dies (‘focus’-patient or not), the GP will fill a 19-item survey on self-perceived quality of care delivered for this patient with a self-assessment for performance and two open questions. This survey was constructed by the research team to reflect the components of the CPPPC and has been minimally validated by informal peer review. The more steps are completed by a GP, the higher the level of involvement in the CPPPC is considered to be.

#### Monitoring quality of care and quality of life

Participating patients will receive a 14-item base-line survey to answer background questions on different psychosocial, cultural and spiritual issues.

Afterwards, every person involved in the study or an appointed relative will receive surveys about quality of life and quality of care periodically. This 26-item survey is an amalgam of adapted versions of the Palliative Outcome Scale (POS) [34] and (POS-S) [35], the NIVEL quality indicators for palliative care [36, 37] and a limited number of questions related to the 7 C’s of the Gold Standard Framework [22]. Several parts of this survey have been validated separately, but not the sum of it. The frequency for this questionnaire is monthly if the PPSv2 score is unknown or more than 30 %, and weekly if the PPSv2 is 30 % or less.

After the death of a participating patient, the appointed relative will fill a 5-item survey on perceived quality of care during and after the dying process.

### Sample size calculation

The average size of the patient population per active GP is estimated to be approximately 1000 [15]. With a mortality of 1 % per year [38], 10 patients per GP per year are expected to die, of which 9 are expected to die non-suddenly [39]. Pre-existing differences are expected to exist between the patient populations of GPs. For instance (although not found in literature), the age of GPs is expected to be positively correlated with the age of his patients, which is relevant for palliative care delivery. On a district level, the availability of health care services [40] and on a socio-cultural level the preferred use of health care services also influence patient outcomes [41]. Therefore, we assume in the following power calculations a relatedness between eligible patients within a GP patient population expressed by an intra-class correlation coefficient of 0.2 and an average of 9 eligible patients per GP.

To detect a difference of 15 % hospital death rate between the trained and the untrained GPs, a classic randomized control trial with two groups, taking into account an intra-class correlation coefficient of 0.2, would require a sample size about 440 GPs to reach 80 % statistical power. Thanks to the stepped wedge design implemented in this study, with 5 clusters, 5 steps and 1 baseline measurement, the required sample size of GPs is reduced to approximately 180, as calculated in a recently published formula [42]. The total number of GPs amenable in this study is approximately 3500. Hence, a participation rate of 5 % is required. This participation rate of 5 % is considered realistically achievable, according to Rogers’ Innovation/Adoption curve (15 % of all people are considered ‘innovators’ and ‘early adaptors’, adapting innovations fast) [43].

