### Stepped wedge cluster procedure

It was decided to have phase intervals of six months, starting from the 1st of April 2013. The first phase is a ‘usual care’ phase for all the clusters. Every next phase, the intervention will be started in one cluster. The last intervention phase (phase 6) lasts until the 31st of March 2016. After this last date, no more ‘interventions’ on behalf of the study will be undertaken: neither meetings or educational sessions or recruitment of GPs and patients for the study.

A post-intervention data collection period for included patients will follow. This period (phase 7) lasts for 33 months, enabling the authors to cope with the effect delay of the intervention: patients will probably not all die in the same phase they were included in the study. Data collection will stop the 31st of December 2018.

A time schedule of the ‘stepped wedge cluster design’ is shown below (Fig. 1).

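### The stepped-wedge sample size uses 9 deaths per GP, an annual figure, for six-month periods that by the plan's own rate yield about 4.5

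*Protocol article*

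**What the plan says.** All inputs are in the protocol article.

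- **Annual deaths.** Under Sample size calculation, a GP population of about 1000 and a mortality of 1 % per year lead to: "10 patients per GP per year are expected to die, of which 9 are expected to die non-suddenly".
- **Input to the power calculations.** The same paragraph ends by assuming "an intra-class correlation coefficient of 0.2 and an average of 9 eligible patients per GP". The unit of time is gone.
- **Parallel-group size.** A two-group trial to detect 15 points "would require a sample size about 440 GPs to reach 80 % statistical power".
- **Stepped-wedge size.** The layout is given as "with 5 clusters, 5 steps and 1 baseline measurement". From this layout the article concludes that "the required sample size of GPs is reduced to approximately 180, as calculated in a recently published formula". It compares the result with about 3500 GPs, a participation rate of 5 %.
- **Length of a phase.** Under Stepped wedge cluster procedure: "It was decided to have phase intervals of six months, starting from the 1st of April 2013". Phase 1 is usual care everywhere, and one region starts in each later phase up to phase 6.
- **After the last step.** "This period (phase 7) lasts for 33 months, enabling the authors to cope with the effect delay of the intervention". It is not one of the five steps.

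**The concern.** In a stepped-wedge calculation the cluster size is the number of subjects each cluster contributes in one measurement period. One baseline and five steps make six periods, which match phases 1 to 6 of the timetable, each six months long. The 9 is a twelve-month count. Nothing in the article supports 9 deaths per GP per phase or a twelve-month period in the formula. On its face, then, the calculation credits each GP with twice the deaths that a phase can deliver.

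The number of GPs, the participation rate and the 80 % power claim all come out of this calculation. A reader who repaired another part of it and kept the 9 would carry the error into the new number.

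**Working it through.** **1. Reproduce the parallel-group figure.** Inputs: 50 % versus 35 %, 80 % power, ICC 0.2, 9 per GP (all printed); two-sided 5 % (assumed, not printed).
- Unadjusted size for two proportions: 170 per arm, 340 in total.
- Design effect: 1 + (9 - 1) x 0.2 = 2.6.
- 170 x 2.6 = 442, against the printed 440.

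This product is a count of patients per arm, although the article labels it GPs. In GPs, a parallel trial with 9 patients each would need 2 x 442 / 9 = about 98 in total.

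**2. Reproduce the stepped-wedge figure.** The cited formula is not available. The usual factor is assumed, with k = 5 steps, b = 1 baseline, t = 1 measurement per step (assumed), r = 0.2 and n subjects per GP per period:

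[1 + r(ktn + bn - 1)] / [1 + r(ktn/2 + bn - 1)] x 3(1 - r) / [2t(k - 1/k)]

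- n = 9: (11.6 / 7.1) x (2.4 / 9.6) = 0.4085, and 440 x 0.4085 = 179.7. The printed value is 180.
- n = 4.5: (6.2 / 3.95) x (2.4 / 9.6) = 0.3924, and 440 x 0.3924 = 172.7.

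The printed value fits 9 per period.

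**3. What the timetable delivers.**
- Per phase: 9 per year x 0.5 year = 4.5 per GP.
- Phases 1 to 6: 6 x 4.5 = 27 per GP, against 6 x 9 = 54 in the formula.

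**4. Effect inside the printed chain.**
- 4.5 in the stepped-wedge factor only: about 173 GPs, and 173 / 3500 = 4.9 %, against 180 / 3500 = 5.1 %.
- 4.5 in both factors: the parallel design effect becomes 1 + 3.5 x 0.2 = 1.7, and 170 x 1.7 x 0.3924 = about 113.

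The figure goes down because the chain never divides by the number of patients per GP. Halving that number therefore carries no penalty.

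**5. Effect in a consistent calculation.** Apply the stepped-wedge factor to the unadjusted 340 patients and divide by n to obtain GPs:
- n = 9: 340 x 0.4085 / 9 = 15.4 GPs.
- n = 4.5: 340 x 0.3924 / 4.5 = 29.6 GPs.

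A direct generalised-least-squares calculation agrees: about 15.5 and 29.7 GPs, a ratio of 1.92. It uses a GP random intercept, fixed period effects, total variance 0.425 x 0.575, ICC 0.2, and GPs spread equally over five steps and all crossing over.

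**6. What this means at 180 GPs, in the same model.**

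| Deaths per GP per phase | Standard error | Detectable difference, 80 % power (2.80 x SE) | Power for 15 points |
|---|---|---|---|
| 9 | 0.0157 | 4.4 points | > 99 % |
| 4.5 | 0.0218 | 6.1 points | > 99 % |

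**The case against.** - **180 GPs are still enough.** This stands. A reader might infer from the doubled count that the trial is under-powered. The documents do not support that: the printed chain moves down when corrected, and in the consistent model 180 GPs far exceed what 15 points requires. Any loss of power computed for about 16 GPs describes a trial that nobody proposed.
- **Phase 7 restores the deaths.** In total it nearly does: 36 + 33 = 69 months at 9 per year is about 52 deaths per GP, against the 54 implied. So the total number of events is not halved. But 33 of those months fall after every region has started, and the printed calculation counts only one baseline and five steps. Phase 7 does not make 9 the right size for a six-month step.
- **The back-calculation does not prove that 9 per period was used.** Correct. The factor is nearly flat in n: 7 per period gives 177.5 and 12 gives 181.7, both close to 180. The formula is unseen, and the significance level and t = 1 are assumed. The stronger evidence is that the article itself names 9 as the input.
- **The model is not the trial's comparison.** Also correct. Under Study population and Analysis, patients of participating GPs are compared with patients of non-participating GPs, matched if possible. The model has no such controls. It also ignores that the steps are taken by only five regions. Its results show the size of the input error and are not the trial's power.
- **The units of the 440 are the larger fault.** Probably so, but repairing them alone and keeping 9 per phase would give about 15 GPs where about 30 are needed. The unit fault currently hides this one.

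**Conclusion.** The point holds as a wrong input. An annual count of 9 is used as the size of a six-month period, where the article's own rate gives about 4.5, a factor of two per phase. Its consequence for the stated plan is limited. The printed 180 would become about 173 or 113, and 180 GPs remain ample for 15 points under the idealised GP-level model, with a detectable difference of about 6.1 points instead of 4.4. The 5 % participation rate hardly moves if only the stepped-wedge factor changes. The importance lies in the repair: once GPs and patients are counted properly, the requirement roughly doubles, from about 15 to about 30 GPs.

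The conclusion that 9 is annual and the phases are six months rests on the text alone. The numerical sizes rest on a two-sided 5 % level, one measurement per step, the usual stepped-wedge factor, and a model in which every GP crosses over.

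**What to change.** In Sample size calculation, state the expected deaths with their time unit: about 9 non-sudden deaths per GP per year, hence about 4.5 per six-month phase. Rerun the stepped-wedge calculation with that per-phase size, and say explicitly how the 33-month phase 7 enters (for example, as a separate, longer period). Correct the units of the 440 in the same step. Then restate the required number of GPs, the participation rate, and the power or the detectable difference.

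The cost is one recalculation and a revised paragraph. No extra recruitment is needed. The stated efficiency per GP becomes less favourable.

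### The 440 GPs given for a parallel trial do not follow from the stated inputs, which give about 440 patients per group (about 98 GPs in total); the 180 GPs and the 5 % target inherit the error

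*Protocol article*

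**What the plan says.** All planning figures are in the protocol article under Sample size calculation.

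- **Effect.** The aim is stated as "To detect a difference of 15 % hospital death rate between the trained and the untrained GPs". The section on the primary outcome fixes the two rates: "The primary outcome of this study is a reduction of all hospital deaths from 50 % [30, 31] to 35" %. The General discussion repeats them.
- **Clustering.** Relatedness within a GP's patients is "expressed by an intra-class correlation coefficient of 0.2 and an average of 9 eligible patients per GP".
- **Source of the 9.** It is an annual count: "10 patients per GP per year are expected to die, of which 9 are expected to die non-suddenly".
- **Parallel design.** A two-group randomised trial that allows for this ICC "would require a sample size about 440 GPs to reach" 80 % power.
- **Stepped wedge.** For five regions entering in 5 steps after a single baseline, the article states that "the required sample size of GPs is reduced to approximately 180, as calculated in a recently published formula" (reference 42). Set against about 3500 GPs, this becomes a required participation of 5 %.
- **Phase length.** The section on the stepped wedge procedure says: "It was decided to have phase intervals of six months".

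The section does not state alpha, sidedness or the allocation ratio, and it does not print the formula from reference 42.

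**The concern.** With 9 deaths per GP, 440 GPs would contribute 3960 deaths. That is far more than a comparison of 50 % with 35 % should need at 80 % power, even with an ICC of 0.2, so the unit attached to 440 is doubtful.

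The paragraph is the article's only sample-size justification. The recruitment target, the participation rate called realistically achievable and the claimed saving from the stepped wedge all rest on it. If the figures do not follow from the inputs, the 80 % power attached to 180 GPs is misdescribed, and a reader of a null result cannot tell what size of effect the study could have excluded.

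**Working it through.** **Inputs from the article:** rates 0.50 and 0.35, power 80 %, ICC 0.2, 9 eligible deaths per GP, 5 steps, 1 baseline, about 3500 GPs. **Assumed:** two-sided 5 %, equal groups, one measurement per step.

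**1. Unclustered size per group (pooled two-proportion formula).**
n = [1.96 × √(2 × 0.425 × 0.575) + 0.8416 × √(0.50 × 0.50 + 0.35 × 0.65)]² / 0.15² = (1.370 + 0.582)² / 0.0225 ≈ 169.3 patients.

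**2. Design effect for clustering by GP.**
1 + (9 − 1) × 0.2 = 2.6.

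**3. Clustered size, which reproduces the article's 440.**
169.3 × 2.6 = 440.2. The unit is patients per group. Rounding n up to 170 first gives 442; the arcsine version gives 439.6 and the unpooled version 433.

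**4. Conversion to GPs.**
440.2 / 9 = 48.9 GPs per group, about 98 in total.

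**5. Can any variant give 440 GPs?**

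| Variant | GPs in total |
|---|---|
| Two-sided, no continuity correction | 96 to 100 |
| One-sided 5 % | 78 to 86 |
| Two-sided, continuity-corrected | 106 |
| 90 % power | about 131 |
| 15 % read as relative (50 % to 42.5 %), two-sided | 400 to 415 |

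The last row comes nearest, but it contradicts the stated 35 %. There is also a bound. If ICC were 1, each GP would count as one patient and the total would be 2 × 169.3 ≈ 339 GPs. A total of 440 needs 2 × 169.3 × (1 + 8 × ICC) / 9 = 440, which gives ICC ≈ 1.34 and is impossible.

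**6. What 440 GPs would deliver.**
220 per group × 9 = 1980 deaths, and 1980 / 2.6 ≈ 762 effective per group. Power for 15 points exceeds 99.9 %. The difference detectable with 80 % power is about 7.2 points.

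**7. Reconstruction of 180.**
The usual closed-form stepped-wedge factor with k = 5 steps, b = 1 baseline, t = 1, n = 9 and r = 0.2 is
[1 + r(ktn + bn − 1)] / [1 + r(0.5ktn + bn − 1)] × 3(1 − r) / [2t(k − 1/k)]
= (11.6 / 7.1) × (2.4 / 9.6) = 1.634 × 0.25 = 0.4085.
440 × 0.4085 = 179.7, which is the article's 180. This factor already contains the ICC and the cluster size, so it belongs on the unclustered total (about 339 patients). The match suggests that it was applied to a number already multiplied by 2.6, not doubled for two groups and not divided by 9.

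**8. Consistency check on the same formula.**
339 × 0.4085 ≈ 138 patients per measurement, about 15 GPs at 9 deaths per period. A six-month phase yields 9 / 2 = 4.5 deaths per GP; the factor is then 0.392 and the result about 30 GPs. Neither is 180.

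**9. What 180 GPs would deliver in a parallel split.**
90 per group × 9 / 2.6 ≈ 312 effective per group, giving about 97 % power for 15 points.

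**10. Participation.**
180 / 3500 = 5.1 %. The division is right, but the numerator is not supported. For comparison, 98 / 3500 = 2.8 %.

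**The case against.** **The route is a reconstruction.** The article shows no working and the cited formula is not available. This stands for the explanation of 180, which should be worded as an inference, although two stated figures reproduce from the article's own inputs. It does not rescue 440 GPs: no tested variant with the stated rates and 80 % power gives that number, whatever the origin of 180.

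**The error is on the safe side.** This also stands. A reader might infer from a faulty calculation that the study is underpowered. The article does not support that reading, because on its inputs more GPs are asked for than needed.

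**The formula's own answer looks like 15 to 30 GPs.** A reader might conclude that so few would suffice. The formula treats GPs as the stepping clusters, and the classical stepped wedge assigns the order at random. Here the steps are five non-randomised regions, GPs volunteer, and the Analysis section compares participating with non-participating GPs. The 15 to 30 only show that the formula does not return 180.

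**The six-month point is secondary.** It changes the factor only from 0.408 to 0.392, and the final data-collection phase lasts 33 months, so 4.5 deaths does not fit every period. This is fair. It remains true that an annual count was used in a design with six-month intervention phases.

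**Conclusion.** The point holds. The stated 440 GPs should read about 440 patients per group, or about 98 GPs in total, so the parallel requirement is overstated about 4.5-fold (440 / 98). The figure of 180 GPs has no valid derivation in the article, and the most likely explanation is a second design effect applied to a mislabelled patient count. The 5 % target inherits this. So does the claim that the stepped wedge reduces the requirement, since the corrected parallel figure of 98 is already below 180.

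The conclusion about 440 assumes a two-sided 5 % test and equal groups; the alternatives tried at 50 % vs 35 % give 78 to about 131 GPs, never near 440. The conclusion about 180 also assumes that reference 42 contains the standard factor. Nothing here shows a shortfall in power. Equally, the 97 % is no assurance for the real study, because it ignores regional clustering and self-selection of GPs.

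**What to change.** Rewrite the second paragraph of Sample size calculation.

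1. Restate the parallel figure as about 440 eligible deaths per group, about 49 GPs per group and 98 in total, with alpha, sidedness and allocation given.
2. Delete the step from 440 to 180 and the claimed saving from the stepped wedge.
3. Keep 180 GPs (5 %) as a recruitment goal if wanted, but do not present it as the number required for 80 % power. Do not put 15 to 30 GPs in its place.
4. Restate power or the detectable difference for the contrast actually planned, participating versus non-participating GPs. Label units (patients or GPs, per group or total), use one design effect, match deaths per GP to the period analysed, and state the control ratio and follow-up as assumptions.

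As an illustration of item 4 only: 180 versus 180 GPs with one year of deaths gives 180 × 9 / 2.6 ≈ 623 effective patients per group, hence about 8 points at 80 % power. The 1:1 control ratio and the single year are assumptions that the article does not make, and the figure ignores regional clustering and self-selection.

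The cost is one paragraph of rewriting and a short recalculation. No additional GPs or patients are needed.

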## Methods/Design

### The stepped wedge cluster design (quasi-experimental)

For this study, a cluster design with a “stepped wedge” approach was chosen. This type of trial design involves sequential roll-out of an intervention to clusters over a number of time periods. The order in which clusters start the intervention is determined at random. In the end, all clusters will have started the intervention. This trial design is particularly interesting 1) when a certain intervention cannot be started simultaneously in all clusters, for instance because of logistical or financial reasons and 2) when researchers want to prevent ethical objections arising from withholding an intervention anticipated to be beneficial [29].

Five clusters will be involved (Table 3). The implementation of the CPPPC will be initiated in all clusters, in a stepped way. Ideally, to reduce bias, the different clusters need to be randomized from the start of the project. However, in this particular study, it was impossible to randomize the order of the regions from the beginning. Not all 5 clusters were well defined at the start of the project. Whenever we found a region’s palliative care network ready to participate, we offered that region the choice to start in the next phase, regardless of any preferences as a research team. That is why this study should be called a quasi-experimental study based on a stepped wedge cluster design.

**Table 3 Tab3:** Characteristics of the five participating clusters, in chronological order of planned start [.]

Cluster	Official language	Nr of inhabitants [46]	PCN/Palliative home care teams situation	GP circles
1: Zone of Antwerp	Dutch	765.470	One legal entity	12, of which 3 not completely in the territory
2: Zone of Mons	French	572.979	One legal entity	8, of 3 which not completely in the territory
3: Brussels Capital Region	Dutch/French	1.163.486	1 PCN, 1 Dutch-speaking and 3 French-speaking palliative home care teams	1 Dutch-speaking + union of 19 French-speaking
4: Province of Limburg	Dutch	856.280	PCN and palliative home care teams separate, residing in the same building	17, of which 1 not completely in the territory
5: Province of Namur	French	484.737	One legal entity	8, of which 2 not completely in the territory

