### Analysis

For the analysis of primary and secondary outcome measures, longitudinal and cluster analysis are to be used to compare data of patient populations of participating GPs vs. patient populations of non-participating GPs. If possible, the IMA will match included GPs with control GPs based on age category (per 5 years) and GP circle. If matching proves not to be realistically achievable, these characteristics of the GPs will be considered independent variables.

The data related to monitoring the implementation of the CPPPC and the quality of care and quality of life, are to be used descriptively to contextualize the primary and secondary outcomes related to participating GPs and patients. To be able to describe the GPs’ patient populations, data will also be available through the IMA on the patients’ age category, gender, month of death, disease category (cancer vs. non-cancer; presence of dementia) and socio-economic status.

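### The 180-GP target rests on a stepped-wedge reduction that fits neither the unit that steps nor the stated contrast, and its starting figure is patients per arm labelled as GPs

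*Protocol article*

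**What the plan says.** All of the following is in the protocol article.

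- **Effect.** Under Primary outcome: "The primary outcome of this study is a reduction of all hospital deaths from 50 % [30, 31] to 35" per cent. The Sample size calculation section takes this as the contrast to be powered: "To detect a difference of 15 % hospital death rate between the trained and the untrained GPs".
- **Clustering.** The same section mentions differences between GPs' patients, between districts and between socio-cultural settings. It then represents them all by one relatedness within a GP's patients, "expressed by an intra-class correlation coefficient of 0.2 and an average of 9 eligible patients per GP".
- **Two-group size.** A randomised trial with two groups "would require a sample size about 440 GPs to reach 80 % statistical power".
- **Reduction.** The section then lowers this to about 180 GPs, giving as the reason: "Thanks to the stepped wedge design implemented in this study, with 5 clusters, 5 steps and 1 baseline measurement". From a pool of about 3500 GPs it derives a required participation of 5 %.
- **What steps.** The design sections name five regions as the clusters. One starts per six-month phase, and for the order of starts "it was impossible to randomize the order of the regions from the beginning". Within a region, GPs are recruited as volunteers through a kick-off workshop and later smaller sessions. Recruitment may continue until 31 March 2016.
- **What is compared.** The Analysis section says longitudinal and cluster methods will be used "to compare data of patient populations of participating GPs vs. patient populations of non-participating GPs", with controls matched on age category and GP circle if possible. The Abstract and the Study population section describe the same comparison.

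**The concern.** A stepped-wedge reduction is earned when each cluster is observed before and after its own switch and the treatment effect is estimated from those switches, with the correlation placed at the level that switches. The sample size section takes the reduction for GPs, while the switching is done by five regions and the stated contrast is between GPs who join and GPs who never do.

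This is the trial's only stated basis for its power and for the 5 % participation target. If the factor and the number it multiplies do not belong to the planned comparison, a reader cannot tell from the article what power 180 GPs provide, in either direction.

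**Working it through.** **Inputs.** Hospital death 50 % versus 35 % (Primary outcome). ICC 0.2, 9 patients per GP, 80 % power, 5 steps and 1 baseline (Sample size calculation). Alpha is not given in that section, so two-sided 0.05 is assumed.

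**1. Patients per arm without clustering.** With mean proportion 0.425:

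n = [1.96·√(2·0.425·0.575) + 0.8416·√(0.50·0.50 + 0.35·0.65)]² / 0.15²
= [1.370 + 0.582]² / 0.0225 ≈ 169.3, rounded up to 170 per arm.

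**2. The 440.** The design effect for GPs as clusters is 1 + (9 − 1)·0.2 = 2.6, and 170 × 2.6 = 442. This matches 440, but the unit is patients per arm. In GPs it is 442/9 = 49.1, so 50 per arm and 100 in total.

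Two cross-checks on the unit:
- 440 GPs with 9 patients each are 3960 patients. Against 2 × 170 = 340 unadjusted patients, that implies a design effect of 3960/340 = 11.65 and an ICC of (11.65 − 1)/8 = 1.33, which is impossible.
- One-sided testing, a continuity correction, unpooled variance or 90 % power give totals between 78 and 140 GPs, never 440.

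**3. The 180.** The article cites a formula without printing it. The standard cross-sectional stepped-wedge design effect, with k steps, b baseline measurements, t measurements per step, n patients per cluster per measurement and ICC ρ, is

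[1 + ρ(ktn + bn − 1)] / [1 + ρ(ktn/2 + bn − 1)] × 3(1 − ρ) / [2t(k − 1/k)].

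With k = 5, b = 1, t = 1, n = 9, ρ = 0.2:
- numerator 1 + 0.2·53 = 11.6
- denominator 1 + 0.2·30.5 = 7.1
- last term 2.4/9.6 = 0.25

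The factor is (11.6/7.1) × 0.25 = 0.408, and 440 × 0.408 ≈ 180. The implied ratio in the text is 180/440 = 0.409. So the n and ρ used were those of a single GP. Nine is also a yearly figure: with 4.5 patients per six-month phase the factor is 0.392 and the result 173.

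**4. What this factor assumes, beside what the article describes.**

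| Assumed by the calculation | Described in the article |
|---|---|
| The cluster of 9 patients with ICC 0.2 (the GP) is the unit that switches at a step | Regions switch; GPs join as volunteers at varying times after their region starts |
| Correlation sits at the level that switches | No region or region-by-phase correlation enters, although district-level influences are named |
| The effect is estimated from clusters that all cross over | Participating GPs are compared with non-participating GPs, who do not cross over |
| The factor multiplies a size not yet adjusted for clustering, because it contains ρ itself | It multiplies 440, already inflated by 2.6 and in patients per arm |

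**5. Power of the plain two-group GP comparison on the stated inputs.** With m effective patients per arm, power = Φ{[0.15 − 1.96·√(0.48875/m)] / √(0.4775/m)}.
- 90 versus 90 GPs: m = 90·9/2.6 = 311.5, power ≈ 0.97.
- 180 participating versus 180 matched controls: m = 180·9/2.6 = 623.1, power above 0.99.

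**The case against.** The Analysis section does say longitudinal. That could cover a before/after element or a model with time-varying exposure, and an article may leave the model's form to the full protocol or analysis plan. This stands to the extent that one cannot say the trial is unable to use its wedge. It does not remove the mismatch. The sentence names only the participating versus non-participating contrast, and the GP-level factor would be wrong even for a region-stepped model, because the stepping level carries no correlation.

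Three stronger readings are tempting, and the documents do not support them.

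- **That without the reduction the trial needs 440 GPs and is badly underpowered at 180.** The 440 is not a count of GPs, and 180 exceeds the 100 that the stated inputs require. Moreover, 180 out of 3500 is the 5 % participation figure, so the 180 appear to be participating GPs only, with controls in addition.
- **That late joining leaves too little exposed time for the comparison.** The documents give no recruitment pattern. The Stepped wedge cluster procedure section also adds a 33-month phase 7 to allow for delayed effects, with consumption data to 31 December 2018.
- **That the non-random order of regions forfeits the saving.** The article discloses the order and lists it as a limitation. It is a question of bias and does not change the variance factor.

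**Conclusion.** The concern holds as an error in the stated justification. The 180-GP target and its 80 % power come from multiplying a mislabelled, already inflated number by a factor of about 0.41 that belongs to neither the unit that steps nor the contrast that is stated.

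No shortfall in power is shown. On the article's own inputs the two-group comparison needs about 100 GPs, and 180 give about 97 % power or more. Those values assume two-sided alpha 0.05, one year's deaths (9) per GP and an ICC of 0.2. They allow nothing for region-level correlation, partial exposure or volunteer bias. The documents give no figure for any of these three, so the true power of the planned analysis remains unknown.

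**What to change.** Correct the units in the Sample size calculation section and say whether 180 counts participating GPs only or both groups. Then restate required size, power and participation rate for the contrast that will be analysed, in one of two ways:

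- **(a)** Remove the stepped-wedge reduction and give power for the two-group GP comparison with design effect 2.6. On the stated inputs that is 442 patients per arm, or 50 GPs per arm.
- **(b)** Commit to a primary model with GP exposure that varies over time, phase and region effects, and non-participating GPs as concurrent controls. Compute power for that model with a GP variance and a region-by-phase variance, the latter over a stated range because the documents give no value.

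The sentence crediting the stepped wedge should stay only under (b), with the recomputed figure. State alpha and sidedness in either case.

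Option (a) costs a short recalculation and rewording; (b) adds the commitment to a model. Neither asks for extra recruitment.
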